In year 6 of the SOS continuation (awarded in 2013), we interviewed participants who received at least three mailed fecal tests but did not complete screening). The most common reason for not screening was related to not paying attention, either by not remembering, not making time for testing, or procrastinating (“out of sight, out of mind”). Other reasons were discomfort with handling stool, putting stool in the mail, and difficulty with dietary restrictions (e.g., in SOS year 3, KPWA\* and SOS switched from a three-sample guaiac test to a single-sample FIT that requires no dietary changes). We also interviewed patients who recently completed their first fecal test, most often the FIT. New users noted: “it was easy to get it done.” Based on our findings, in year 6 of SOS, we added back the nurse navigator (automated mailings + navigation) to address concerns and personalize screening. However, nurse navigation is expensive compared to automated mailings. If inattention is the primary reason for not testing or not trying the new test without dietary restrictions, financial incentives might help increase CRC screening in harder-to-reach populations. We propose testing this hypothesis.

We know of only one study that tested the comparative effectiveness of financial incentives for patients who complete fecal testing. Kullgren et al conducted a study at a Veterans Administration (VA) clinic in Philadelphia, enrolling 1549 patients due for CRC screening in a two-part study. In part 1, patients were assigned to usual care or to receive \$5, \$10, or \$20 for fecal occult blood test (FOBT) completion. In part 2 (based on the results of part 1), patients were assigned to usual care or to receive \$5, \$10, a 1 in 10 chance for \$50, or entry into a \$500 raffle for FOBT completion. Three sample guaiac fecal kits were handed out in clinic and included a brightly colored index card with the pre-assigned incentive for completion. No significant differences in FOBT completion were seen between the groups, except for the group assigned a 1 in 10 chance for \$50. FOBT completion at 30 days was 49.3% versus usual care 29.7% ( $P < 0.001$ ). Limitations included participation by men only (>99%), use of an older three-sample test, and lack of comparisons by subgroups.

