We will send letters to 5000 potentially eligible patients describing the study with a brief survey to collect sociodemographic information and confirm eligibility. Questions will be from the main SOS study and are based on the Preventive Health model that predicted screening in our main SOS and other studies, asking about self-efficacy, pros and cons of fecal testing, social influence, and “defensive information processing” (e.g., “I like to ignore the fact that I could get cancer”), which specifically addresses avoidance and inattention to screening. We will include a \$2 bill with the survey (based on evidence that this increases participation rates) to thank recipients for their time.

Based on our prior SOS ARRA Supplement (testing adherence to 3 types of fecal test kits), we expect 29% to return the survey and 23% to be eligible and enrolled, with a target enrollment of 1150 participants (two-thirds non-white or Hispanic and one-third Medicaid [white or non-white]). We will use a computer-based randomized sequence generator to assign patients to: (1) Mailed; (2) Mailed plus \$10; or (3) Mailed plus Lottery. Randomization will be stratified by history of prior CRC testing (yes/no based on electronic data), white vs. non-white race or Hispanic, or Medicaid status (yes/no) to ensure balance by these key characteristics. The randomization sequence will be concealed to everyone except the study programmer. Outcomes will be blinded until data collection is complete.

A second set of 5000 potentially eligible patients will receive mailings as described. Additionally, Kaiser Permanente Washington Health Research Institute’s (KPWHRI) Survey Research Program staff will conduct one reminder call to patients who do not return a survey after 14-21 days (approved by the KPWHRI Institutional Review Board on 6/12/2017). When respondents are available, the caller asks if they received the survey and if they have any questions. The patient may request another packet be mailed or refuse participation in the study at that time. The caller will ask for the survey to be returned within two weeks. When another person answers but the patient is not available, the caller leaves a message that they are calling from KPWHRI about a study and requests the best time of day to call again. If the caller receives an answering machine, a voicemail is left with a phone number to request a new questionnaire.

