### **6. Study Procedures**

7. The study programmer will identify eligible using KPWA virtual warehouse data.
  - The study programmer will identify eligible subjects using the KPWA virtual warehouse data
  - The KPWHRI Survey Research Program will mail an invitation letter, information sheet describing the study (Page 11), survey (Page 14), and a \$2 incentive to potential participants.
  - If interested, potential participants return the survey in a-postage paid envelope to the Survey Research Program.
  - In the second wave of recruitment, patients who do not return a survey will be called by Survey staff 14-21 days after receiving the survey to remind them to return it.
  - The Survey staff confirm eligibility of individuals who return their survey. We will not follow up with people who return a survey and are found to be ineligible.
  - The study programmer will perform randomization using a concealed automated computer-generated program with participants assigned to one of three intervention groups.
  - Intervention groups
    - Group 1:** Survey staff will mail participants a pamphlet on CRC testing choices and a letter stating that they will soon receive a FIT kit in the mail, and a number to call if they prefer another option. One week later, Survey staff will mail a second letter, FIT kit, pictograph, wordless instructions, and a postage-paid return envelope. A reminder letter will be sent to participants not completing the FIT kit after 3 weeks.
    - Group 2:** These participants receive the same intervention as group 1 with the following modifications: Mailing 1, the letter will include notification that they will receive \$10 (cash) as a thank you for completing testing (FIT, flexible sigmoidoscopy, or colonoscopy) within 6 months. Mailing 2 (FIT kit with letter and wordless pictograph instructions) and mailing 3 (reminder letter for those still not returning kits) will include the same information about the \$10 thank you for CRC screening completion. Mailing 4 will include a thank you and \$10 for those who complete screening.

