| BMI                                                                                                                                                                                                                                                                                                                             |        |                           |                   | X            | Last recorded      |
| Charlson Co-morbidity                                                                                                                                                                                                                                                                                                           | X      |                           |                   | X            | 2016               |
| Utilization, primary care visits, preventive visits                                                                                                                                                                                                                                                                             |        |                           |                   | X            | 2017               |
| 
* Data will be kept on participants and non-responders to determine the representativeness of study participation. No data will be kept on individuals refusing participation (calling the research number to opt out).
           CRC = colorectal cancer; flex sig = flexible sigmoidoscopy; BMI = body mass index
 |        |                           |                   |              |                    |

We will also collect basic demographic data on non-responders (Sample sociodemographic column above). We will not keep identifiers except for census block data. We will destroy all other identifiers as soon as enrollment is completed.

A study aim is to determine if financial incentives decrease screening disparities. We need to know the representativeness of participants to evaluate this. We will compare the sociodemographic characteristics of participants to non-participants to determine the generalizability of our results, particularly for characteristics that pertain to groups with known screening disparities (non-white race, Hispanic ethnicity, Medicaid insurance, and younger age, i.e., aged 50-64)

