## 8. Data Analysis

### Analysis Plan

**Primary Outcome:** The primary outcome is CRC screening within the 6 months following randomization (yes/no). We will use electronic data to measure outcomes, which we previously demonstrated as highly valid for accurately capturing CRC tests. We will report the number and percent screened by randomization group. Generalized linear models with logit link and robust variance estimator will estimate the probability of screening. We will use predictive margins based on these logistic models to estimate differences in screening rates between randomization groups. Models will adjust for age, sex, race/ethnicity, education, and screening history prior to randomization. With a targeted enrollment of 1150 participants, we will have 80% power to detect a 10% net difference in CRC screening uptake among randomization groups.

**Secondary Analyses** will explore whether the effect of incentives on screening uptake differs by race/ethnicity, Medicaid coverage, income, education, sex, and history of prior CRC testing. Interaction terms between these variables and the intervention group will be included in multivariable models, and Wald tests will be used to assess the overall significance of effect modification.

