**8. Considering your life right now, how important is it for you to get screened for colon cancer in the next 6 months?**

- ☐ Very important
- ☐ Somewhat important
- ☐ Not very important
- ☐ Not at all important

People can have many different reasons why they do not want to get screened for colon cancer. On a scale from 1 to 5, please tell us how much you agree or disagree with the following reasons for not getting screened for colon cancer.

**It would be difficult for me to be screened for colon cancer because...**

Strongly  
Disagree

[figure not shown]

Strongly  
Agree

|                                                                                          |   |   |   |   |   |
|------------------------------------------------------------------------------------------|---|---|---|---|---|
| 9. The test might find something wrong.                                                  | 1 | 2 | 3 | 4 | 5 |
| 10. It is too embarrassing.                                                              | 1 | 2 | 3 | 4 | 5 |
| 11. The stool blood test might be disgusting.                                            | 1 | 2 | 3 | 4 | 5 |
| 12. There might be unexpected costs or bills to pay.                                     | 1 | 2 | 3 | 4 | 5 |
| 13. I have other priorities right now, but I will eventually get colon cancer screening. | 1 | 2 | 3 | 4 | 5 |
| 14. I don't think I need it because I don't think I will get colon cancer                | 1 | 2 | 3 | 4 | 5 |

Now we would like to know what would make you **want** to get screened for colon cancer. On a scale from 1 to 5, please tell us how much you agree or disagree with the following reasons **to get screened** for colon cancer.

**I want to get screened for colon cancer because ...**

Strongly  
Disagree

[figure not shown]

Strongly  
Agree

|                                                                  |   |   |   |   |   |
|------------------------------------------------------------------|---|---|---|---|---|
| 15. Finding cancer early gives me a better chance at a cure.     | 1 | 2 | 3 | 4 | 5 |
| 16. Receiving clear findings would give me peace of mind.        | 1 | 2 | 3 | 4 | 5 |
| 17. My family would be happy if I got screened.                  | 1 | 2 | 3 | 4 | 5 |
| 18. Getting screened is part of taking care of myself.           | 1 | 2 | 3 | 4 | 5 |
| -19. The benefits of getting screened outweigh the difficulties. | 1 | 2 | 3 | 4 | 5 |

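### The primary model leaves out the baseline attitude scores that the protocol links to screening, forgoing a small, low-cost gain in precision (minor, optional)

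*Protocol*

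**What the plan says.** The Analysis Plan (Section 8, Data Analysis) fits a logistic model with robust variance and uses predictive margins to estimate differences in screening rates between arms. On covariates it states: "Models will adjust for age, sex, race/ethnicity, education, and screening history prior to randomization". On size it states: "With a targeted enrollment of 1150 participants", "we will have 80% power to detect a 10% net difference in CRC screening uptake among randomization groups".

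Section 4 (Study Design) says that the survey questions are "based on the Preventive Health model that predicted screening in our main SOS and other studies". It names self-efficacy, pros and cons of fecal testing, social influence and defensive information processing. Returning the survey is the route into the trial, so the answers are collected before randomization. The survey itself (Section 15) tells respondents that they may skip any question. Questions 21 to 24 ask how confident the respondent is about steps towards screening. I read these as the self-efficacy items, although the survey does not label them so.

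The Analysis Plan lists six effect modifiers for the secondary analyses: race/ethnicity, Medicaid coverage, income, education, sex and prior testing. No attitude score appears there or among the covariates.

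**The concern.** A baseline variable that predicts the outcome can be added to a predictive-margins model without changing what is estimated. The quantity remains the difference in screening rates between arms, and its standard error falls. Here the candidate variables are already collected before randomization, and the protocol itself ties them to screening. The calculated power sits close to 80% with little margin, so even a small gain has some value for each pairwise contrast. At stake is precision only. The validity of the comparison is not in question.

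**Working it through.** **Inputs.** Total 1150 and three arms are from the protocol (Analysis Plan and Section 6). The protocol gives no allocation ratio, alpha, sidedness or Mailed-arm rate with the power statement. I assume equal allocation (1150/3 = 383.3 per arm), two-sided 5% per pairwise comparison, and a range of Mailed-arm rates.

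**Step 1: reproduce the stated 80%, without covariates.** Two-proportion test, pooled variance under the null, no continuity correction, 10-point difference:

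| Mailed vs incentive | Power |
|---|---|
| 30% vs 40% | 82.8% |
| 40% vs 50% | 79.6% |
| 45% vs 55% | 79.2% |
| 50% vs 60% | 79.6% |
| 60% vs 70% | 82.8% |

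The least favorable of these cases needs 392 per arm, or 1176 in total, for 80% power. That is within 3% of 1150. The stated power therefore does not depend on the omitted scores.

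**Step 2: gain from adding one score.** Take 50% vs 60% with unpooled variance:

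- SE = sqrt((0.25 + 0.24)/383.3) = 0.03575
- z = 0.10/0.03575 = 2.80
- power = Φ(2.80 − 1.96) = 79.9% (the pooled form in Step 1 gives 79.6%)

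Let the added score be standard normal and independent of the listed covariates, with a given odds ratio per SD in a logistic model at an overall rate of 55%. The added share of outcome variance explained is R² = Var(p(x))/(p(1 − p)). The SE is multiplied by sqrt(1 − R²), and the equivalent sample size is 1150/(1 − R²).

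| Odds ratio per SD (assumed) | R² | SE reduction | Power | Equivalent extra participants |
|---|---|---|---|---|
| 1.3 | 1.6% | 0.8% | 80.5% | 19 |
| 1.5 | 3.8% | 1.9% | 81.4% | 45 |
| 1.75 | 6.8% | 3.4% | 82.6% | 83 |
| 2.0 | 9.8% | 5.0% | 83.8% | 124 |

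The gain is 80.5 − 79.9 = 0.6 points at the low end and 83.8 − 79.9 = 3.9 points at the high end.

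**Step 3: check with the planned estimator.** I simulated a logistic model with predictive margins, 383 per arm, 45% vs 55%, with a score for the listed covariates already in the model. Adding a survey score with odds ratio 1.22, 1.49, 1.82 or 2.23 per SD cut the variance by about 1%, 3%, 6% or 13%. The mean estimate stayed at about 0.10 with and without the score. This agrees with Step 2.

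**Step 4: skipped items.** If participants with a missing score were dropped, effective n would be n(1 − m)/(1 − R²), where m is the fraction lost. The gain vanishes when m = R². At 45% vs 55% with R² = 5%, power is 81.2% with no loss, 79.2% with 5% lost and 77.0% with 10% lost. If each item were skipped by 1% of people independently (an assumption), four items would cost 1 − 0.99⁴ = 3.9% of complete cases, and twenty would cost 1 − 0.99²⁰ = 18%. The score must therefore be short, and nobody should be dropped for skipping it.

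**The case against.** The strongest reply is that nothing here is an error. A short prespecified covariate list is valid, the stated power holds without the scores, and the size of the gain rests on odds ratios that the protocol does not supply. Screening history, probably a strong predictor, is already in the model. Education, also in the model, is itself a survey item, so the survey is not ignored. Items can be skipped, so the gain is not free. All of this stands. It limits the point to a minor one but does not remove it, because a missing-answer category deals with skipped items and the remaining cost is small.

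A reader might infer more than the documents support, in four ways.

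- *That the trial never tests its own inattention rationale.* The Background ends that argument with "We propose testing this hypothesis", but the hypothesis is that incentives may raise screening in harder-to-reach groups. Inattention is the condition attached to it. The primary analysis and the planned interactions with race/ethnicity, Medicaid and prior testing address those groups. A statistical analysis plan, not at hand, may also contain exploratory work on the scales.
- *That an interaction built from survey questions 13, 35 and 36 would test inattention.* Section 4 ties inattention to defensive information processing. Nothing supports those three items as a scale.
- *That survey question 8 is an obvious covariate.* It asks "Considering your life right now, how important is it for you to get screened for colon cancer in the next 6 months". That measures importance rather than intention, and it is not a construct that Section 4 names.
- *That the data row "Utilization, primary care visits, preventive visits", dated 2017, is a mis-dated baseline covariate.* The protocol never assigns it that role, and Section 6 lists these data among those collected at the end of 6 months.

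**Conclusion.** The point holds as a minor, optional improvement. The protocol fixes a primary model without any pre-randomization attitude score, although it says the survey rests on a model that predicted screening. The loss is about 0.6 to 4 power points, or a standard error 0.8% to 5.0% larger than it could be. This rests on an assumed odds ratio of 1.3 to 2.0 per SD beyond the listed covariates, equal arms, two-sided 5%, rates of 50% vs 60%, and no participants lost to skipped items. If the score adds little beyond screening history and education, the gain is close to zero. There is no bias, no contradiction in the text, and no effect on the stated power.

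**What to change.** In the Analysis Plan, add one short score from a construct named in Section 4 to the primary covariate list. The mean of the answered items among survey questions 21 to 24 would serve. Add a 'not answered' category for those who skip all four, so that no participant leaves the analysis. Fix the scoring rule before outcomes are unblinded, and keep predictive margins as the effect measure.

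The cost is a sentence or two of analysis wording, one or two more model degrees of freedom, and a stated rule for skipped items. No new data or participants are needed. If the sponsor prefers the present list, it is valid as it stands.

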## 1. Protocol Title

### Financial Incentives to Increase Colorectal Cancer Screening in Priority Populations

## 2. Objectives

We propose to build on the success of the Systems of Support to Increase Colorectal Cancer trial (SOS, R01CA121125, [name]) and focus on disparity groups who are less likely to be current for CRC screening. We will test whether financial incentives increase screening uptake and decrease screening disparities. Usual care for CRC screening at Kaiser Permanente Washington (KPWA, previously Group Health Cooperative) includes giving fecal immunochemical test (FITs) to patients at clinic visits and mailing FITs during patients' birthday month.

We will send letters and a questionnaire to 5000 patients aged 50-75 who are not current for CRC screening, inviting them to participate in a study to increase screening. Using race, ethnicity, and insurance coverage electronic health record (EHR) data, two-thirds of those invited will be identified as non-White race or Hispanic ethnicity or having Medicaid coverage. The other third will be white and have non-Medicaid insurance coverage. Invitees who return the survey and remain eligible (estimated N = 1150) will be randomized to either (1) Mailed fecal immunochemical test (FIT) kit, or mailed FIT kit *plus* one of two types of financial incentives for completing testing: (2) a guaranteed Monetary incentive (\$10), or (3) probabilistic Lottery incentive (1 in 10 chance for \$50). Our primary outcome will be completion of CRC screening within 6 months. Secondary analyses will assess whether the effect of incentives on screening completion rates differs by race/ethnicity and Medicaid coverage.

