### Limitations and Strengths:

- Although we have sufficient power to test our primary outcome, overall differences in CRC screening uptake at 6 months for either Monetary or Lottery incentives compared to Mailed only, we will not have sufficient power to test differences by subgroup (race, ethnicity, low income). We will be able to compare the magnitude of effects by subgroups and generate hypotheses for further study.
- All patients have health insurance and, similar to the Northwest, the overall population is primarily white. However, we will assure adequate representation of disparity populations (at least two-thirds) by oversampling from non-white and Medicaid patient populations.
- Intervention materials will be designed for low levels of literacy (including the use of wordless FIT test instructions developed for the STOP CRC study ([UH3CA188640, [name], [name]]), but not culturally tailored to specific race, ethnicity, and language groups. Subsequent studies could explore this further.
- Offering financial incentives sometimes raises ethical concerns, especially when specifically offered to disadvantaged populations. Yet we argue that we are studying a health equity issue and some groups need additional support to achieve the same health outcomes of more advantaged groups. We work with several Medicaid insurance providers (not within KPWA) who have been providing monetary incentives to patients for completion of fecal testing, but who do not know if this strategy is effective. We have consulted our Institutional Review Board. They reviewed the study design and had no objections.
- Our study is ambitious given the limited funding provided by the supplement. Because of the parent grant we will be able to efficiently recruit, implement, and evaluate the proposed study. We received an ARRA administrative supplement (CA121125-A2, [name]) with similarly ambitious goals, and achieved our targeted enrollment and completed all study aims with results published promptly at the end of the funding period.

20

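### The disparity aim is worded in screening rates but assessed by interaction tests on the odds-ratio scale, which do not directly say whether the rate gap narrows

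*Protocol*

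**What the plan says.** Section 2 (Objectives) sets the aim: "We will test whether financial incentives increase screening uptake and decrease screening disparities". The data-collection part of Section 6 repeats it: "A study aim is to determine if financial incentives decrease screening disparities". Section 2 puts the secondary question in terms of rates and names two modifiers: "Secondary analyses will assess whether the effect of incentives on screening completion rates differs by race/ethnicity and Medicaid coverage".

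Section 8 (Analysis Plan) specifies a generalized linear model with logit link for the primary outcome and turns it into a rate difference: "We will use predictive margins based on these logistic models to estimate differences in screening rates between randomization groups". The secondary paragraph then asks whether the effect "differs by race/ethnicity, Medicaid coverage, income, education, sex, and history of prior CRC testing", and gives the method as follows: "Interaction terms between these variables and the intervention group will be included in multivariable models, and Wald tests will be used". It names no scale for the interaction. Predictive margins are mentioned only for comparisons between randomization groups, not within or between subgroups.

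The limitations part of Section 8 says that power is insufficient for subgroup differences, that the size of effects will be compared across subgroups, and that the results serve to generate hypotheses.

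**The concern.** The protocol describes disparities as differences in the percentage screened: Section 4 gives the share of members up to date by race, ethnicity and Medicaid, and Table 1 gives rates by race/ethnicity in the prior trial. With the main effect also a rate difference, the natural target for the disparity aim is the change in the rate gap between groups when an incentive is added.

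A product term in a logistic model is the log of a ratio of odds ratios. Testing it against zero is a different hypothesis from no change in the gap whenever the groups start from different rates. A null interaction can go with a narrowing or a widening gap, and an unchanged gap can appear as an interaction. At stake is whether the reported result answers the disparity question that the trial was set up to address.

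**Working it through.** **Plan's own figure.** Section 8 claims 80% power for a 10-point difference with 1150 participants. Assume equal allocation (1150/3 = 383.3 per arm) and two-sided 5% for one pair of arms. Then z = [0.10 − 1.96·√(2·p̄(1−p̄)/n)] / √[(p1(1−p1) + p2(1−p2))/n]. At 50% versus 60%: (0.10 − 1.96 × 0.0359)/0.0358 = 0.83, so power is 79.6%. For baselines of 40% to 55% it lies between 79.2% and 80.8%. The stated figure reproduces for the main comparison and is not in question.

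**Scale comparison.** The protocol gives no Mailed-only rates by subgroup for this trial, so the rates below are assumptions shown over a range. With odds = p/(1−p), a common odds ratio (OR) of 1.5 moves p to 1.5·odds/(1 + 1.5·odds). For 72%: odds 2.571 become 3.857, a rate of 79.4%. For 55%: odds 1.222 become 1.833, a rate of 64.7%. The last column takes the opposite case, a 10-point gain in both groups (gap unchanged), and gives the less-screened group's OR divided by the better-screened group's.

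| Assumed Mailed-only rates | Rates at common OR 1.5 | Gap before → after (points) | Gap change | Ratio of ORs if both gain 10 points |
|---|---|---|---|---|
| 72% / 55% | 79.4% / 64.7% | 17.0 → 14.7 | −2.3 | 0.86 (1.52 / 1.77) |
| 60% / 50% | 69.2% / 60.0% | 10.0 → 9.2 | −0.8 | 0.96 |
| 51% / 50% | 61.0% / 60.0% | 1.0 → 1.0 | 0.0 | 1.00 |
| 40% / 30% | 50.0% / 39.1% | 10.0 → 10.9 | +0.9 | 1.04 |
| 29% / 17% | 38.0% / 23.5% | 12.0 → 14.5 | +2.5 | 1.15 |

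Sources of the pairs:
- 72%/55%: white and Medicaid shares up to date with screening in Section 4.
- 51%/50%: Automated (mailed) arm of Table 1, white versus non-white or Hispanic.
- 29%/17%: usual-care arm of Table 1, same groups.
- The other two are round values.

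So a true null for the planned test can go with a gap that narrows, stays or widens, depending on where the groups start. Near 50% in both groups the scales agree.

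**Precision of a gap change.** Take one incentive arm against Mailed, a two-thirds/one-third split (255.6 and 127.8 per arm) and a variance of 0.24 per person. SE = √[2 × 0.24 × (1/255.6 + 1/127.8)] = √0.00563 = 0.075, or 7.5 points. The change detectable with 80% power is about 2.80 × 7.5 = 21 points. For a 10-point gap change at assumed rates of 50% to 70%, power is about 26% to 28% for the rate-gap contrast and 24% to 27% for the interaction on the log-odds scale.

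**The case against.** The strongest reply is that the discrepancy is small and may be absent here. The 72% and 55% are shares of all members who are up to date, whereas every enrollee is overdue, so they are not Mailed-only uptake. The closest mailed-arm figures in the protocol are the 51% and 50% of Table 1, where the scales coincide. The 29%/17% pair comes from usual care, and this trial has no usual-care arm. This stands and is why the rates are labelled assumptions. It does not settle the matter: Table 1 reports two-year adherence in a different sample and has no Medicaid row, so similar starting rates cannot be taken for granted here.

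Second, changing scale gains no power. The two tests perform alike, and a 2.3-point gap change against an SE of 7.5 would be detected about 6% of the time. This also stands. The gain is an interpretable estimate, not a more sensitive test.

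Third, the analyses are declared exploratory, and such detail is often left to an SAP, which is not at hand. The status is correct and limits the weight of the point. But the protocol does state a method, and on the natural reading its scale differs from that of its own question. The plan to compare the size of effects across subgroups also needs a scale.

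A reader might infer a multiplicity problem from the six listed modifiers, since 1 − 0.95^6 = 26.5% for six independent tests at 5%. The protocol does not support that reading: it does not say whether the modifiers are fitted separately or together, and it does not present the tests as confirmatory.

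**Conclusion.** The point holds in a limited form. The stated interaction tests do not directly answer whether the gap in screening rates narrows. In the examples above the two scales differ by 0 to 2.5 points at an odds ratio of 1.5, with the direction depending on baseline, against an SE of about 7.5 points. The mismatch is unlikely by itself to decide a conclusion, but correcting it costs almost nothing.

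The conclusion rests on two readings. The interaction terms are taken to sit in the logistic model, because no other model is named; the secondary paragraph says only that the models are multivariable. A disparity is taken to be a gap in rates, because the protocol describes it that way; it gives no formal definition.

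Two stronger readings are not supported. A reader might see a contradiction between the aim in Section 6 and the power caveat in Section 8, but the first states a purpose and the second qualifies what can be concluded; any rewording is editorial. A reader might also conclude that the trial needs one lead contrast pooling both incentives and comparing the whole oversampled group with the rest. Section 2 names race/ethnicity and Medicaid as the modifiers, and the comparison of lottery with guaranteed payment is central to the rationale in Section 3, so pooling would be a debatable preference.

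**What to change.** In the secondary-analysis paragraph of Section 8, specify the following from the same logistic models with the interaction terms, for race/ethnicity and Medicaid:

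- predictive-margin screening rates by arm within each subgroup;
- for each incentive arm separately, the between-group difference in the incentive-minus-Mailed rate difference, with 95% CI.

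Treat the second item as the main disparity result. The Wald interaction tests may stay beside it. Report income, education, sex and prior testing as exploratory estimates.

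The cost is a little extra analysis; no further data or participants are needed. The intervals will be wide, roughly ±1.96 × 7.5 = ±15 points under the split assumed above, and wider if a subgroup is smaller. That fits the hypothesis-generating status the protocol already gives these analyses.
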